#### Background, context and socio-demographic variables

Where necessary, we will account for socio-demographic variables (such as age, gender, marital status, number of children, education in years, and household income) and other context variables including COVID-19 related questions (e.g., access to green spaces, job status, covid-related health status, living situation, financial and job risk factors etc.) assessed in the context of the extensive assessment in phase 1. Predictive value of relevant context- and demographic variables on differences in variables of interest at pretest and their training-related change will be explored similarly to the prediction by latent trait factors assessed in phase 1. Besides, initial levels on outcome variables of interest at pretest will be controlled for by including autoregressive paths in respective models.

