
An estimated 300 individuals, 100 per intervention group, will be recruited. A priori effect size and power calculations have been performed based on the results from the previous mental training study, the ReSource project [67], which developed and validated the interventions being applied in the current study. Power analyses were conducted using G*Power [194] for analysis of variance with repeated measurements and interactions between group and intra-group variables. The analyses elements were as follows: an alpha level of .05, with a power (1-ß) of .80, 3 groups and 2 measurement occasions, a correlation of variables with repeated measurements of .39 which is the lower limit of retest reliability for the Cortisol Awakening Response (CAR; [195]), and an assumed small effect size of *f* = .10. This results in a total sample size of *n* = 297. For the additional third measurement time (post-test 2 following socio-emotional intervention given to waitlist control group) power analysis was conducted in a similar manner as above.

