#### Effects of mental training interventions on pre-post changes in variables of interest

In order to evaluate intervention-related effects on variables of interest, a mixed-effects modeling approach will be applied. Effects of time of assessment (pre-test/post-test for primary outcome variables and pre-training session/post-training session for secondary outcome variables respectively) and intervention group (socio-emotional mental training/mindfulness-based mental training/waitlist control group), as well as the interaction between time and group will be defined as fixed effects. Dummy coding with the waitlist control group as reference will be used for the intervention group variable. Additionally, we will control for participant-related random effects.

In addition, latent change scores for each primary outcome variable respectively will be computed with two timepoints (pre-test/post-test). The change in outcomes will be modeled as a latent variable and this latent change will be predicted by the treatment condition (path c in Fig 6). A correlation between the latent change score and initial levels on the primary outcome variable of interest is evaluated.

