#### Prediction of pretest and intervention-related changes in variables of interest by trait-level individual characteristics and changes in state-levels of vulnerability, resilience and social cohesion

Further, we are interested in exploring whether certain individuals respond better or worse to the interventions based upon specific trait characteristics as well as trajectories of state-level psychological vulnerability, resilience and social cohesion during the course of the pandemic in phase1 (T1-T7). For this, data from phase 1 of the CovSocial project will be used. Phase 1 data has been previously analyzed using a latent factor model approach for trait vulnerability, resilience and social cohesion, and latent change score models for changes in state vulnerability, resilience and social cohesion. Standardized latent factor scores obtained from the trait and state factor models constructed and published in phase 1 (Silveira et al., in preparation) will be used in our current mixed effects modeling approach. Please see preregistration of phase 1 for further details on what indicators constitute the trait and state vulnerability, resilience and social cohesion factors (osf.io/jvb98).

We will examine whether trait predispositions predict mental state at pretest and moderate pre-post intervention changes in the current phase 2 of the project (‘trait effect’). Latent change factors will be employed as outlined above. Observed primary outcome variables at pretest as well as latent changes of those outcome variables will be regressed on the latent trait factors.Next, we will evaluate whether state changes in stress and vulnerability, resilience and social cohesion during the pandemic (T1-T7) can predict state variables of interest at pretest and intervention-related changes in phase 2. Four different models of latent change will be computed using phase 1 data:

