“Acute first lockdown effect”: The change in latent factors from pre-lockdown to the first lockdown will be determined using latent change score models (T1-T2 in phase 1)“Recovery effect”: The change in latent factors from the first lockdown to re-opening in Berlin will be determined using latent change score models (T2-T3)“Second lockdown fatigue effect”: The trajectory of change in latent factors during the second lockdown in Berlin will be indicated by the latent slope in latent growth curve models (T4-T7)“Cumulative pandemic effect”: We will compute an unweighted sum of standardized latent change score “acute first lockdown effect” and the standardized latent slope “second lockdown fatigue effect”

Observed primary outcome variables at pretest as well as latent change scores of those outcome variables will be regressed on these latent change scores (acute first lockdown effect, recovery effect), latent slopes (second lockdown fatigue effect), and unweighted sum of the change trajectories (cumulative pandemic effect).

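### The plan does not settle whether models predicting outcome change condition on the observed pre-test; if they do, non-randomised predictors of level can appear to predict change

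*Protocol article*

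**What the plan says.** All references are to the protocol article, mostly to its statistical analysis plan.

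- **Trait predictors** (section on prediction of pretest and intervention-related changes): "Observed primary outcome variables at pretest as well as latent changes of those outcome variables will be regressed on the latent trait factors". The section states the aim as moderation of pre-post intervention change. It takes over the latent change factors outlined earlier, and says the Phase 1 factor scores "will be used in our current mixed effects modeling approach".
- **Pandemic trajectories** (same section): "Observed primary outcome variables at pretest as well as latent change scores of those outcome variables will be regressed on these latent change scores". The same is planned for the second-lockdown slope and the cumulative sum.
- **Demographic and context variables** (section on background, context and socio-demographic variables): "their training-related change will be explored similarly to the prediction by latent trait factors assessed in phase 1".
- **Handling of the pre-test** (same section): "initial levels on outcome variables of interest at pretest will be controlled for by including autoregressive paths in respective models".
- **Change score** (section on effects on pre-post changes): change is formed from two waves, with no multiple-indicator measurement model described. Its link to the starting level is given as follows: "A correlation between the latent change score and initial levels on the primary outcome variable of interest is evaluated".
- **Reliability** (Sample and sampling procedure): the only figure is "a correlation of variables with repeated measurements of .39 which is the lower limit of retest reliability", for the cortisol awakening response.

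No predictor-by-group term is written out for any of these models.

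**The concern.** Adjusting for the pre-test is sound for a randomised contrast, because group is independent of the person's stable level. Phase 1 traits, lockdown trajectories and income are not randomised, and the plan itself expects them to relate to pre-test status. An observed pre-test is a fallible reading of the stable level. Conditioning on it removes only part of that level, and a predictor related to the level takes up the rest as an apparent effect on change.

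The correlational form in the pre-post section does not condition on the pre-test and has no such artefact under a stable level. The two sections can therefore give different results from the same data, and the article does not say which will be reported. At stake are statements about which people change more or less over training. The Discussion sets out to answer whether specific risk groups benefit more from one type of intervention.

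**Working it through.** **The plan's own figure.** Inputs from the power paragraph: f = .10, 3 groups, 2 occasions, correlation .39, α = .05, power .80. The noncentrality is f²·N·m/(1 − ρ) = .01 × 297 × 2/.61 = 9.74, with 2 and 294 degrees of freedom. Power is 0.8002, and 297 is the smallest multiple of 3 that reaches 80%. The stated N reproduces, and .39 acts there as the pre-post correlation.

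**The artefact.** Let pre-test, post-test and predictor have unit variance. Let the predictor correlate r with both waves (no change in anyone), and let pre and post correlate at the retest value ρ.

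- Change regressed on predictor and pre-test: the predictor's coefficient is (r − rρ)/(1 − r²) = r(1 − ρ)/(1 − r²).
- Change regressed on the predictor alone: r − r = 0.
- Predictor-by-group: the first coefficient is the same in every randomised arm, so its difference between arms is 0.

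Examples: ρ = .39, r = .2 gives .2 × .61/.96 = .127; ρ = .80, r = .3 gives .3 × .20/.91 = .066.

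**False-positive rates.** Simulation with N = 300, group dummies included, two-sided α = .05, 1,500 runs per cell. Only ρ = .39 comes from the document; every r and every other ρ is assumed.

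| ρ | r | coefficient | pre-test controlled | pre-test not controlled | predictor-by-group, pre-test controlled |
|---|---|---|---|---|---|
| .39 | .1 | .062 | 21% | 5.2% | 5.6% |
| .39 | .2 | .127 | 65% | 5.4% | 4.5% |
| .39 | .3 | .201 | 96% | 5.3% | 4.3% |
| .60 | .2 | .083 | 41% | 5.3% | 4.9% |
| .60 | .3 | .132 | 79% | 5.5% | 5.2% |
| .80 | .2 | .042 | 21% | 5.5% | 4.3% |
| .80 | .3 | .066 | 42% | 4.8% | 5.7% |
| .90 | .2 | .021 | 13% | 4.9% | 4.8% |
| .90 | .3 | .033 | 25% | 5.3% | 5.6% |

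Separate runs gave 61% at ρ = .39, r = .2, and 22% and 44% at ρ = .80 for r = .2 and .3. With r = 0 the rate is nominal, and with ρ = 1 the coefficient is 0.

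**Pandemic trajectories.** The table assumes a stable level plus independent noise. Phase 1 ran to March 2021 and the first pre-screened participant was invited on 27 May 2021, so a person's state may carry over into the pre-test. With an assumed autocorrelated state (autocorrelation .3–.7, state variance .4–.6), no training effect, and the T4–T7 change as predictor, unadjusted change rejected in 16–39% of trials and adjusted change in 5–10%. Over further assumed settings the ranges were 9–84% and 6–28%. The predictor-by-group test stayed at 3–7%.

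**The case against.** The strongest reply is that the biased model is inferred. The prediction section refers back to the latent change factors already outlined, where change and initial level are correlated. Regressing both pre-test and change on the predictor with that correlation is unadjusted change. The sentence on autoregressive paths names no specific model, and a path fixed at 1 merely defines the change score and does no harm. This stands in part. The sentence gives control of initial levels as its purpose, which favours a free path, but the text does not settle it. A reader might infer that the plan is committed to a model that finds change where there is none. The documents support only an unresolved conflict, with that consequence under one reading.

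The reply on size also stands. The .39 is a lower limit for one outcome. At that retest an observed r of .2 or .3 implies a correlation with the stable level of .2/√.39 = .32 or .3/√.39 = .48, and nothing in the article supplies such values. A reader might infer that almost any Phase 1 predictor would be flagged; 13% at ρ = .90, r = .2 does not bear that out.

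Nor do the mixed model and the adjusted change model give opposite answers. They give zero and non-zero under the null, which are different answers. The personalisation conclusions would be spurious only if they rested on the predictor's main effect. The stated aim of moderation points to a group interaction, which is unaffected, but that term is not written out.

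Finally, unadjusted change is not safe for every predictor, as the carry-over results show. A latent pre-test built from same-occasion parcels is not a full cure either. At ρ = .39, r = .3 and an assumed internal consistency of .8, the coefficient is (.3 × .8 − .3 × .39)/(.8 − .09) = .17, against .20.

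**Conclusion.** The concern holds as a conflict to be reconciled, with a material consequence under the freely estimated reading. In that case a non-randomised predictor related to the stable level shows an effect of r(1 − retest)/(1 − r²) on change when nobody changes. False positives at N = 300 are about 61–65% at retest .39 with r = .2 (cortisol awakening response, lower limit), and about 12–44% at assumed retests of .8–.9 with r = .2–.3.

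This rests on three conditions: the predictor relates to the stable level, the observed pre-test carries error or occasion-specific variation, and the path is free.

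The point is of moderate weight. The randomised group comparison is untouched, and the article presents these analyses as exploratory. That label does not protect the reader, since every hypothesis is tested at α = .05 and the findings are meant to inform who benefits from which training.

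**What to change.** 1. Reconcile the section on pre-post changes with the section on background, context and socio-demographic variables. State for each model whether the autoregressive path is fixed or free.
2. Keep the autoregressive adjustment for the randomised group effect.
3. Base every statement about who responds to training on the predictor-by-group term (time-by-predictor-by-group in the mixed model) against the waitlist group. It is nominal with or without pre-test adjustment.
4. For the main effect of time-stable traits and demographics on change, use the correlational form: pre-test and change both regressed on the predictor, with correlated residuals.
5. For pandemic-trajectory predictors, do not interpret the main effect on change as training-related under either model.

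The cost is wording only; no new data are needed. The downside is precision. With equal variances, the standard error of a slope difference between two arms of 100, relative to a pooled slope in 300, is √(1/100 + 1/100)/√(1/300) = √6 ≈ 2.4 times as large. Many moderator results will therefore be imprecise and should be reported as such.

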## Discussion

The current study aims to examine the impact of online socio-emotional and mindfulness-based interventions on stress, loneliness, social connectedness, mental health, psychological resilience, and social capacities and cohesion in the context of the current SARS-CoV-2 pandemic. Several empirical studies have provided strong evidence for poor mental well-being outcomes owing to the very high levels of stress and isolation generated as a result of the pandemic and the related lockdowns. The massive social changes induced due to measures such as physical distancing and closure of arenas of social participation, have not only impacted individual levels of stress and vulnerability, but also ushered a change in crucial societal foundation of social cohesion. Therefore, the current study will assess whether brief online interventions aimed at enhancing mental well-being, psychological resilience and social cohesion can reduce individual stress, loneliness and vulnerability and enhance individual psychological resilience, and also improve social capacities and cohesion amongst the various elements of society.

The current study adapts socio-emotional and mindfulness-based interventions applied in the ReSource project (67). The project applied intensive, 3-month long, in-person practice of mindfulness-based and socio-affective interventions that led to enhancement of mental well-being, social capacities such as compassion, empathy and prosocial behaviors, and reductions in a range of vulnerability factors such as stress or negative affect (68). In the current study, we plan to test whether such interventions can be beneficial and have measurable effects when delivered in a less intense, purely app-based online format, with only 12 minutes of practice per day over only a few weeks. This could allow for the development of more flexible forms of such interventions to be able to apply these on a larger scale to heterogeneous population samples. As such, we will validate whether brief, daily 12-minute online interventions that last 10 weeks can lead to prevention of maladaptive outcomes such as depression, anxiety, loneliness and stress, and lead to enhanced resilience, mental well-being as well as increased social competencies and cohesion. This will allow us to ascertain whether large-scale application of such interventions, that require minimal time and effort from participants, is feasible or not in terms of application and outcomes. The findings from the present study will also allow us to test whether such brief interventions can be applied to more clinical settings to reduce incidence of development of psychological disorders, such as major depression and generalized anxiety, in the face of more global stressors. Also, two associated questions of interest that will be answered are a) which type of mental training intervention is specifically effective in bringing about changes in which outcomes, and b) whether specific risk groups benefit more from one specific type of mindfulness-based or socio-emotional intervention. Moreover, the study will also clarify whether the biological embedding of stressful experiences, in the form of genotypic and polygenic risk markers of vulnerability, resilience and social cohesion, can be changed or reversed upon undergoing mindfulness-based and socio-emotional interventions. Lastly, the present study will also serve to advance the field of digitalized and personalized mental health interventions, which is increasingly being seen as an alternative to more traditional forms of in-person psychotherapy and interventions.

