**Discussion:**

Results will reveal the differential effectiveness of two brief online interventions in improving mental health outcomes, as well as enhancing social capacities and resilience. The present study will serve as a first step for future application of scalable, low-cost interventions at a broader level to reduce stress and loneliness, improve mental health and build resilience and social capacities in the face of global stressors.

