### Interventions

#### Socio-emotional mental training (group 1)

The behavioral intervention will consist of 10 weeks of daily Affect Dyad practice with a partner as the core exercise. In the Affect Dyad (AD), participants perform a 12-minute partner-based exercise which involves contemplating over the experience of one difficult situation and one situation which incurred gratitude in the past 24 hours. Both partners take turns speaking about the two situations while the other partner listens in a non-judgmental manner. While the participants elaborate on the situations, they are asked to mostly focus on the bodily experience of the emotions generated during the situation. Daily practice of the dyad begins with a moment of silence wherein participants are required to center themselves and let go of the events and feelings experienced during the day thus far. After this, the first partner speaks about a difficult or stressful situation they experienced during the past 24 hours, and the emotions arising in that situation were felt in their body. While the first partner speaks, the other partner remains silent and is instructed to listen in an empathic non-judgmental manner. After speaking for 2.5 minutes about the difficult situation, the first partner then speaks about a situation that made them feel grateful or gratitude experienced in the past 24 hours, and how the emotions arising during this situation were felt in their bodily sensations. The partner once again remains silent and listens with an empathic and non-judgmental stance. Once the first partner finishes speaking about the grateful situation for 2.5 minutes, the entire procedure is then repeated with the second partner as speaker and the first partner as listener. The exercise ends with a moment of silence once again. Participants perform this daily exercise 6 times a week. Prior to each week of daily dyad practice, the participants are randomly paired to one other participant in the Affect Dyad group. The goal of the exercise is to enhance coping with difficult emotions, increase social connectedness, (self) acceptance, empathic and non-judgmental listening and gratitude.

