#### Mindfulness-based mental training (group 2)

The behavioral intervention will consist of 10 weeks of daily individual attention-based mindfulness meditation practice. One of the core practices will be Breathing Meditation (BM), a 12-minute individual exercise that requires participants to focus their attention on the sensations of breathing. Participants have to sustain their attention to breath for long stretches of time, and have to return their attention to their breath when their mind wanders. Participants will also engage in other practices, such as attention-based mindfulness on sounds (object of attention is sounds in the environment) and open presence meditation (object of attention is sensations present in the inner and outer environment). Daily practice of the meditation takes place through pre-recorded exercise audios recorded by meditation trainers who guide the participants through the entire 12-minute exercise. The exercise begins with participants being asked to sit in a comfortable position that makes them relaxed yet keeps them awake and aware. They are asked to feel the contact to all the objects that their body rests on, and are asked to cultivate an attitude of dignity and receptivity towards themselves and their body. The exercise encourages them to focus their attention on their breath, and to bring back their attention to the breath when their mind has become distracted or has wandered. The key focus of these practices is on training present-moment attention and interoceptive body awareness.

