After the recruitment, participants will complete a 2-week pre-intervention EMA, wherein they will provide saliva samples at specific timepoints and answer questions about their mental and physical health during those corresponding timepoints. This period of data collection will take place at the convenience of participants (at their home, workplace, etc.) to be able to capture the ecologically valid CAR and stress response. For this portion, participants will be sent the appropriate saliva collection kits by mail. Next, all participants will then be invited to the lab to complete the pre-intervention assessment of the behavioral tasks, and they will also complete the pre-intervention assessment of questionnaires using the web and mobile App. This pre-intervention assessment period will last approximately 4 weeks, after which the intervention period will begin.

The intervention period will last 10 weeks, and no blinding will be employed During each week participants in the two intervention groups will perform the intervention-specific exercises 6 times a week using the mobile or web app designed for the study. Every day prior to and after completing the intervention exercise, participants will complete the intervention-related daily EMA using app. Once a week, participants will undergo 2-hour online coaching sessions with an intervention instructor. The purpose of these so-called “weekly check-ins” would be to ensure that participants are able to share insights gained during the week, resolve issues faced during the week, and to keep up the motivation and commitment of participants. Once a week, at a random timepoint, participants will also complete the weekly assessment measures tracking changes in various potential mechanistic variables of interest using the app. During this first intervention period, participants in the retest control group will not complete any daily EMA or weekly assessments. After the completion of the first 10-week intervention period, all participants will again be invited to the lab to complete the same battery of behavioral tasks at post-intervention, and will also complete the same battery of questionnaires through the web and mobile App. Participants will once again undergo a 2-week post-intervention EMA period, during which they will provide saliva samples at specific timepoints, along with answering questions about mental and physical health at those timepoints.

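### The Discussion promises a conclusion about a purely app-based, minimal-time format, but the waitlist contrast tests app practice plus 2 hours of instructor coaching a week

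*Protocol article*

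**What the plan says.** The Discussion describes the format under test as a "less intense, purely app-based online format, with only 12 minutes of practice per day over only a few weeks". It goes on to say that the results will settle whether large-scale use of interventions "that require minimal time and effort from participants" is feasible.

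The sections on delivery describe more than that:

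- **Procedure, practice:** "participants in the two intervention groups will perform the intervention-specific exercises 6 times a week using the mobile or web app".
- **Session length:** 12 minutes in both arms. In the socio-emotional arm "participants perform a 12-minute partner-based exercise"; in the mindfulness arm breathing meditation is "a 12-minute individual exercise that requires participants to focus their attention on the sensations of breathing".
- **Procedure, coaching:** "Once a week, participants will undergo 2-hour online coaching sessions with an intervention instructor". The stated aims are to let participants share what they have learned, to sort out problems and to maintain motivation.
- **Instructor training:** besides using the app, each participant is assigned to one of four MBSR-trained teachers, who introduce the training, coach its basics and run the weekly check-ins.
- **Retest control group:** in the first 10-week period this group is tested before and after, and nothing else. The Procedure section gives it coaching only in the second period, together with its own training.
- **Statistical analysis plan, pre-post changes:** group is dummy coded with the waitlist as reference.

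**The concern.** A contrast with a waitlist estimates the effect of everything the trained arm receives and the waitlist does not. Here that is two components, and the Discussion's description of the format mentions only one of them. If a trained arm improves more than the waitlist, the improvement could come from the daily exercise, from two hours a week with an instructor, or from both. No arm receives one component without the other.

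This matters because several outcomes, such as loneliness, perceived stress and mood, could plausibly respond to regular contact with an instructor. The article's own rationale sharpens the point: the introduction presents condensed app formats as the answer to longer programmes that demand much time and staff, instructor hours included. A positive waitlist contrast, reported in the terms of the Discussion, would credit the app format with a result obtained with substantial instructor involvement.

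**Working it through.** **Inputs**

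| Quantity | Value | Where stated |
|---|---|---|
| Practice sessions per week | 6 | Procedure |
| Length of one session | 12 min | the two intervention sections |
| Coaching per week | 2 h = 120 min | Procedure |
| Duration | 10 weeks | Procedure |
| Coaching for the waitlist before post-test | none | Retest control group; Procedure |

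**Scheduled time per week**

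- Practice: 6 × 12 = 72 min.
- Coaching: 120 min, which is 120 − 72 = 48 min more than practice (ratio 120/72 = 1.67).
- Together: 192 min = 3.2 h, against the 72 min = 1.2 h that the Discussion's description implies.

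**Over 10 weeks**

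- Practice: 72 × 10 / 60 = 12 h.
- Coaching: 2 × 10 = 20 h.
- Coaching share: 20 / (20 + 12) = 62.5%.

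**Sensitivity.** If the 12 minutes a day is taken literally as seven days a week, practice is 7 × 12 = 84 min a week, or 14 h over 10 weeks. Coaching is still longer (120/84 = 1.43), and its share is 120/204 = 58.8%. Practice would equal coaching only at 120/12 = 10 sessions a week.

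**What each contrast estimates**

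| Contrast, pre-test to post-test | Differs in daily practice | Differs in scheduled coaching time |
|---|---|---|
| Socio-emotional v waitlist | yes | yes, 20 h v 0 |
| Mindfulness v waitlist | yes | yes, 20 h v 0 |
| Socio-emotional v mindfulness | yes | no, 20 h v 20 h |

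With the waitlist as reference, the two group-by-time coefficients are the first two rows. The third row is the difference between those coefficients, so it comes from the same fitted model.

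**Sample size.** The stated total of 297 does not depend on this point. It also reproduces: the noncentrality is f²·N·m/(1 − ρ) = 0.01 × 297 × 2 / 0.61 = 9.74 on 2 and 294 degrees of freedom, which gives power 0.8002 at α = .05; N = 294 gives 0.7959.

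**The case against.** The best defence is that comparing a package with a waitlist is a legitimate design and that the coaching is openly described in the article. The figure of 12 minutes of practice per day is literally correct for the exercise, and the sessions are online, so neither that figure nor the word online is wrong. The lower intensity is judged against multi-month programmes with retreats, and by that standard it is fair. Contact hours are also not a measure of therapeutic dose. All of this stands. It leaves untouched the conflict between the purely app-based, minimal-time description and the weekly 2-hour sessions, and the consequence for the waitlist contrast.

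A reader might infer more than the documents support:

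- **That the coaching is costly and cannot be scaled.** No cost or group size is given. With about 200 trained participants and four teachers there would be about 50 each if shared equally; one-to-one sessions would take 50 × 2 = 100 h per teacher per week, so group delivery is likely. That is itself an inference.
- **That scalability is the whole purpose of the trial.** The abstract and the opening of the Discussion put effects on mental health, resilience and social capacities first.
- **That the abstract makes the same error.** Its reference to "scalable, low-cost interventions" concerns future application, with this study as a first step.
- **That the design can say nothing about the daily practice.** The comparison of the trained arms is not confounded by amount of coaching.
- **That failing to mention attendance records is a fault.** An article may leave that to the full protocol.

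**Conclusion.** The point holds for the waitlist contrasts and for the Discussion's description of what is tested. Those contrasts estimate app practice plus instructor coaching, with 20 h of coaching and 12 h of practice scheduled. They cannot support an efficacy or feasibility conclusion about a purely app-based, minimal-time format. How much of any effect coaching would account for is unknown; the 62.5% is a share of scheduled time, not of effect.

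This rests on three readings:

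- The participants who receive weekly coaching in the first period are the two trained groups. This follows from the surrounding text of the Procedure section and from the restriction of the control group to testing.
- Sessions take place as scheduled. The hours leave out the app assessments.
- Coaching time is equal in the two trained arms. Its content may differ, and their comparison speaks to relative effects only.

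The weight is moderate: no estimate changes, but a stated conclusion does.

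**What to change.** Reconcile the Discussion with the Instructor training and Procedure sections:

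1. Describe the tested intervention as app-based daily practice plus a weekly 2-hour online session with an instructor, and drop the purely app-based description.
2. Limit the efficacy and feasibility conclusions drawn from the waitlist contrast to that package, and give the scheduled time as about 3.2 h a week before assessments.
3. Base claims about the specific daily practice on the comparison of the two trained arms, worded as differences between practices.

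The cost is a few sentences and a narrower scalability claim. Design, sample size and analysis stay as they are.
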